## Methods: participants, interventions, and outcomes

### Study setting {9}

Participants will be undergraduate students at public and private universities in Colombia and Mexico, beginning with Universidad Cooperativa de Colombia, la Red de Universidades la Salle, Universidad Autónoma Metropolitana, and Universidad Nacional Autónoma de México. However, it is expected that several more universities will be added. Students will be recruited both from the university student mental health clinics and from the general population of non-help seeking students.

### Eligibility criteria {10}

All undergraduate students at the participating universities that are at least 18 years of age and who screen positive for elevated depressive and/or anxious symptomatology will be eligible to participate irrespective of whether they also present symptomatology of other CMDs like adult ADHD, substance use disorders, and PTSD. Exclusion criteria include any one of the following: (1) screening positive for possible bipolar disorder, (2) report having received a diagnosis of psychosis, or (3) are considered to have serious suicide risk based on self-report of suicide ideation with current intent.

### Who will solicit informed consent? {26a}

Consent procedures were approved by the IRB of the Instituto Nacional de Psiquiatría Ramón de la Fuente Muñiz, the coordinating center. For students recruited from the university mental health clinics, the intake person at the clinic will identify potential study participants when the participants ask for an appointment and will describe the study and answer any questions. Subsequently, interested students will be sent an email invitation and link to the study. Students recruited from the representative samples generated from the list of enrolled students or from those who responded to announcements on the university social media platforms will receive an email that describes the study with an attached study brochure and will be offered to receive a phone call if they would like to ask more questions or receive an explanation from the study team. All students will be able to provide consent online.

### Additional consent provisions for collection and use of participant data and biological specimens in ancillary studies {26b}

If we decide to do an ancillary study in the future, we will seek prior consent of participants to be re-contacted and re-consent for the ancillary study following IRB approval; we do not collect any biological samples.

### Interventions

#### Explanation for the choice of comparators {6b}

CBT is recommended as a first-line treatment for depression and anxiety [34]. iCBT is becoming increasingly common in high-income countries [35] for many reasons including insufficient psychotherapists trained in CBT, the advantages in terms of accessibility (convenience in schedule and travel), empowerment (increased sense of control and psychological ownership), and reduction of barriers (reduced cost, logistical barriers, wait times, and discretion for those who are embarrassed to seek help). Several iCBT programs, both guided and unguided with and without modules to address comorbid disorders, have been developed, implemented, and evaluated (for reviews, see [36–38]). The online platform chosen here, developed by SilverCloud Health, is widely used both commercially (e.g., [39]) and in research (e.g., [27, 40, 41]). It encompasses a wide range of programs, treating an array of conditions from insomnia and stress to comorbid depression and anxiety. The specific program we will use (called *Space from Depression and Anxiety* in the English version) was modified specifically for Latin American college students for this study. This modification was based on a prior cultural adaptation developed for Colombia [42] for a depression-only version translated as *Yo Puedo Sentirme Bien* [“I can feel good” in English]. This name was evaluated in focus groups to be more culturally appropriate than the direct translation. Cross-cultural principles were considered, in which focus group discussions were conducted with Mexican and Colombian students to evaluate the relevance of the personal stories, photos and linguistic expressions in the program, and also expert review of the same content. We will compare the unguided versus guided versions of iCBT to TAU to cover a continuum of least resource intensive/greater self-care options to the more standard highly dependent of professional resources options.

#### Intervention description {11a}

The guided and unguided iCBT interventions delivered through the SilverCloud platform can be accessed through the web interface or by downloading a smartphone app. The program comprises 7 core modules and 9 supplemental modules (see Table 1 for a description) that implement evidence-based CBT strategies for cognitive restructuring, behavioral activation, and relaxation training. The program uses the same techniques as face-to-face CBT, but these are communicated to the user via written text, graphics, videos, and interactive tools. Sessions consist of texts, testimonials, audios, educational video clips, and interactive quizzes, exercises, and homework. The platform is available 24/7 and the users are recommended to complete one module per week. In the case of the guided version, supporters (described further below) welcome users to the platform upon signup and thereafter provide weekly asynchronous written feedback on the activity and tools that users have undertaken on the platform and provide personalized recommendations of content for the users. Supporters can also suggest that users revisit some sections, practice further certain exercises, or unlock access to the supplemental modules to address concomitant difficulties (such as sleep, self-esteem, the COVID pandemic, etc.) based on open-ended text provided by users, thus tailoring the program to each user’s needs. This support in the form of weekly written messages sent through the platform lasts for 8 weeks, but users can continue to access the program for 12 months. Supporters will be bachelor-level graduates of psychology or behavioral health programs who have been trained in the SilverCloud platform and in how to deliver feedback. The content of the unguided version is the same as the guided version, but there is no supporter to provide weekly feedback. Students in the TAU arm will receive whatever service their university normally provides. We will not control the content of TAU, which could be medication, psychotherapy, or referral to a community treatment provider, but we will document this content for use in post hoc analyses. During the COVID-19 pandemic, most university services have been modified to provide online one-on-one psychotherapy via videoconferencing platforms.

**Table 1 Tab1:** SilverCloud iCBT modules, goals, and activities

Modules	Goals	Activities

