## Trial design {8}

First, we will conduct a three-arm single-blind parallel assignment individually randomized equal allocation controlled pragmatic trial on *n* = 1500 students. It will compare aggregate effects of unguided iCBT, guided iCBT, and TAU at 90 days and 12 months. Consistent with previous research, we hypothesize that guided iCBT will have superior aggregate treatment effects to unguided iCBT, but as this will be an initial study that combines novel treatments, methods of treatment delivery, and new ways of matching treatments to students, we were not able to draw on prior theory or research to hypothesize whether the aggregate treatment effects of iCBT will be superior to those of TAU. However, we hypothesize that comparative effectiveness across the three arms will vary significantly by student baseline socio-demographic, environmental, and clinical characteristics,

This initial trial will be followed by two additional trials using the same recruitment methods and same interventions but differing in allocation rules. In the second trial, 25% of n = 1000 students will be individually assigned to the treatment estimated by the PTR in the first trial to yield an optimal short-term response for the student, with the remaining 75% randomized with equal allocation across all 3 treatments. In the third trial, 25% of n = 1000 students will be individually assigned to the treatment estimated by the PTR in the first trial to yield an optimal 12-month probability of remission for the student, with the remaining 75% randomized with equal allocation across all 3 treatments. We hypothesize that students assigned to the treatment recommended by the PTRs will have significantly better outcomes than those randomized across types of treatment. These additional trials will provide a direct evaluation of the value of the PTRs.

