We will report adjusted mean differences (AMDs) with design-adjusted 95% CIs (confidence intervals) and use Poisson regression with robust variance estimation for binary outcomes and report adjusted prevalence ratios (aPRs) with 95% CIs. We will calculate numbers needed to treat (NNTs). When data are missing, we will provide thorough summaries of reasons for missingness and proportions of missing data, test for differences in the characteristics of patients with and without missing data, and describe these and the implications of missing data for interpretation when we report results. As our IPW approach to missing outcomes data will be based on a missing-at-random (MAR) assumption, sensitivity analysis will be carried out based on the weaker missing-not-at-random (MNAR) assumption using pattern mixture modeling [85] in a generalized mixed model framework [86]. The predictors of success in obtaining outcome data at time *t* will include information obtained in prior waves of data collection along with data on intensity of efforts needed to obtain outcome data in a discrete-time survival framework (i.e., in response to the 1^st^, 2^nd^, or 3^rd^ telephone attempts). A range of assumptions about the distribution of the missing data will be made in this approach to investigate sensitivity of results [87]. We will record and report distributions and correlates of dropout and account for all patients in reports.

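### Guided students share supporters but the stated binary-outcome analysis names no cluster unit: if supporters differ in effect and this is ignored, intervals for the guided contrasts will be too narrow

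*Protocol article*

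**What the plan says.** Intervention description {11a}: supporters in the guided arm "provide weekly asynchronous written feedback on the activity and tools", recommend content to each user and can unlock supplemental modules. "This support in the form of weekly written messages sent through the platform lasts for 8 weeks". "Supporters will be bachelor-level graduates of psychology or behavioral health programs"; their number, caseload and assignment to students are not stated. In the unguided version the content is the same but "there is no supporter to provide weekly feedback".

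Trial design {8}: students are randomized individually with equal allocation, and "we hypothesize that guided iCBT will have superior aggregate treatment effects to unguided iCBT". No direction is stated for iCBT against TAU.

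Analysis of aggregate intervention effects (under {20a}): adjusted mean differences are reported with "design-adjusted 95% CIs", a term that is not explained. For binary outcomes the plan is to "use Poisson regression with robust variance estimation for binary outcomes" and to report prevalence ratios with 95% intervals. The GLM error structure for continuous outcomes is left to diagnostics. The only mixed model is in the sensitivity analysis for data missing not at random, and no supporter effect is named there.

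Expected effect size and power calculations (under {14}): there is no ICC, caseload or design effect.

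**The concern.** Supporters have discretion over what they write, recommend and unlock. If some are more effective than others, students with the same supporter will have correlated outcomes. This happens in the guided arm and not in the unguided arm, so the design is partially nested despite individual randomization.

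Robust variance in a Poisson model for a binary outcome corrects for the wrong error distribution. Unless a cluster unit is named, it is by default computed student by student and takes no account of correlation within supporter. Remission is also the outcome on which the protocol evaluates power, because it regards it as clinically the most important.

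At stake is the precision claimed for guided versus unguided, the comparison that bears on whether human support is worth providing. Guided versus TAU is affected in the same way. Unguided versus TAU is not affected by supporters.

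**Working it through.** **The plan's own figure.** The protocol says that fewer than 150 per arm suffice for aggregate effects (power .80, two-sided .05, after loss to follow-up). For remission of 30% against 15%, with pooled variance:

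n = [1.96·√(2 × .225 × .775) + 0.8416·√(.30 × .70 + .15 × .85)]² / .15² = (1.157 + 0.489)² / .0225, which rounds up to 121 per arm.

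This becomes 121/.85, or 143, at 15% loss and 121/.81, or 150, at 19% loss. Response of 50% against 25% needs 58. The figure therefore reproduces, and it does so with no allowance for clustering.

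**Inputs for the clustering check**
- 500 students per arm: protocol, {14}.
- Two-sided .05: protocol, {14}.
- Caseload m of 10, 25 or 50 students, that is 50, 20 or 10 supporters for 500 guided students: assumption.
- Supporter ICC of .01, .02 or .05: assumption. The protocol gives no value.

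**Formulas.** Only the guided arm is clustered; the comparator is not. Outcome variances are taken as equal.
- Design effect in the guided arm: DE = 1 + (m − 1) × ICC
- True over student-level standard error: R = √[(DE + 1)/2]
- Actual level of a nominal 5% test of no average effect: 2 × [1 − Φ(1.96/R)]

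**Worked case.** m = 25, ICC = .02: DE = 1 + 24 × .02 = 1.48; R = √1.24 = 1.114; 1.96/1.114 = 1.76; level 7.8%. Correct intervals would be 11% wider.

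| Caseload (supporters) | ICC | DE | R | Actual level |
|---|---|---|---|---|
| any | 0 | 1.00 | 1.000 | 5.0% |
| 10 (50) | .01 | 1.09 | 1.022 | 5.5% |
| 10 (50) | .02 | 1.18 | 1.044 | 6.0% |
| 10 (50) | .05 | 1.45 | 1.107 | 7.7% |
| 25 (20) | .01 | 1.24 | 1.058 | 6.4% |
| 25 (20) | .02 | 1.48 | 1.114 | 7.8% |
| 25 (20) | .05 | 2.20 | 1.265 | 12.1% |
| 50 (10) | .01 | 1.49 | 1.116 | 7.9% |
| 50 (10) | .02 | 1.98 | 1.221 | 10.8% |
| 50 (10) | .05 | 3.45 | 1.492 | 18.9% |

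**Power when clustering is respected.** Using the protocol's simulation rates of 27.5% and 17.5% with 500 per arm, SE = √[(.275 × .725 × DE + .175 × .825)/500] and power = Φ(.10/SE − 1.96).
- DE 1: SE .0262, power 96.8%.
- DE 1.48: SE .0296, power 92.1%.
- DE 1.98: SE .0328, power 86.1%.
- DE 3.45: SE .0408, power 68.8%.

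These rates are for iCBT against control, so they bear on guided versus TAU. The protocol gives no assumed difference between guided and unguided.

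**What the calculation leaves out.** It uses a normal approximation, which is optimistic when there are only about ten supporters. Loss to follow-up would shrink analysed caseloads and reduce the effect somewhat.

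**The case against.** The strongest reply is that the protocol nowhere says its errors are at student level. Robust variance can be clustered, the design-adjusted intervals may be meant to cover supporters, the GLM error structure is open, and a full protocol or SAP could settle the unit. For mean differences this largely stands: the wording leaves room for a correct analysis. It is weaker for prevalence ratios, where a specific variance method is named without a unit. It is true that an adjective not repeated before the second interval does not prove that design adjustment was excluded there.

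Second, a reader might infer that the test is invalid under any null. It is not. Supporters act only after individual randomization. If guidance changes nobody's outcome, supporters create no correlation and the level stays at 5%. The inflation belongs to a null of zero average effect with supporters who differ, regarded as a sample from a wider pool. That is the natural reading if results are to guide other universities, but it is a choice.

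Third, a reader might infer that TAU students are unclustered. The protocol lets TAU include psychotherapy and says most services now offer one-on-one online sessions, so TAU students may share therapists. The partially nested description is secure for guided versus unguided and less so for guided versus TAU.

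Fourth, the trial was sized for heterogeneity of treatment effects and not for guided versus unguided, and in the case worked above intervals widen by only 11%. That limits the consequence without removing it.

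**Conclusion.** The point holds conditionally. Guided outcomes are nested in supporters, the analysis named for binary outcomes states no cluster unit, and the sample size text makes no allowance for clustering. If the supporter ICC exceeds 0 and supporter is not the cluster unit, intervals for guided versus unguided and guided versus TAU will be too narrow. Across the assumed range the true level runs from about 5.5% to 19%, and correct intervals would be 2% to 49% wider. At ICC 0 nothing changes.

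The documents do not support saying outright that the intervals are too narrow: supporter number, caseload and ICC are all unstated, sharing is itself an inference (though a safe one with about 500 guided students), and mean differences may already be covered. Nor is guided over unguided the trial's only directional hypothesis, since Trial design {8} also predicts better outcomes for students assigned by the precision treatment rule; it is the only one between arms. The point is not extended to the CV-TMLE analysis, for which no variance method is stated. It is firmest for the prevalence ratios in guided versus unguided. It should be put right, but it does not undermine the trial.

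**What to change.** 1. Record the supporter ID of each guided student and carry it into the de-identified analysis file. The measures listed from the platform logs (under Process measures) are logins, time spent and modules entered; supporter ID is not among them.
2. For guided versus unguided and guided versus TAU, use a partially nested analysis: either robust variance clustered on supporter with a small-sample correction, or a supporter random effect in the guided arm only. Apply it to prevalence ratios and mean differences alike.
3. Define the term design-adjusted, and say that it includes supporter clustering and applies to both kinds of outcome.
4. Treat each unguided student as a cluster of one. Do the same for TAU students only if sharing of clinic therapists is judged negligible, and state that judgement.
5. State that supporters are regarded as a sample from a wider pool, so that the null being tested is clear.

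The cost is one stored variable and a few lines of text. No more students are needed. Intervals for the guided contrasts become somewhat wider, more so if supporters are few.

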**1. Getting Started**		
	• Learn about CBT • Learn about depression and anxiety • Introduce the Mood Monitor • Introduce the CBT Cycle • Learn how thoughts, emotions, physical sensations, and behaviors affect each other • Introduce personal stories • Connect with the present moment	• Mood Monitor • My CBT Cycles • Staying in the Present (Breathe) • Depression and anxiety Myths & Facts Quiz • Establishing goals
**2. Noticing Feelings**		
	• Learn about emotions and role in CBT Cycle • Recognize emotions that are difficult to cope with • Recognize physical sensations • Identify activities to target distressing physical sensations associated with depression and anxiety • Explore the impact of lifestyle choices on emotions and well-being • Relate to personal stories	• Emotions & Your Body Quiz • My CBT Cycles • Mapping Lifestyle Choices • Staying in the Present (Progressive Muscle Relaxation)
**4. Boosting Behavior**		
	• Learn about the link between mood and behaviors • Improve knowledge of common behavioral traps and how to beat them • Learn tips on how to get motivated during periods of low mood • Recognize the importance of pleasurable activities and achievements in boosting mood • Relate to personal stories	• Mood & Behavior Quiz • Your Backup & Support Network • My Motivational Tips • My Activities • Your Mood & Your Body • Activity Scheduling • Staying in The Present (Mindful Eating)
**5. Spotting Thoughts**		
	• Learn about the role of thoughts in depression and anxiety within the CBT Cycle • Recognize negative automatic thoughts • Understand and recognize thinking traps • Relate to personal stories	• Me & My Thoughts Quiz • My CBT Cycles • Staying in the Present (Watching Thoughts)
**6. Challenging Thoughts**		
	• Learn about hot thoughts and how to recognize • Learn to challenge negative thoughts • Learn how to overcome specific thinking traps • Recognize situations where it is necessary to use thoughts to cope	• Your Thinking Style Quiz • My Helpful Thoughts • My CBT Cycles • Staying in the Present (Watching Thoughts)
**7. Bringing it Together**	• Preparation for coming to the end of the program • Recognize the importance of social support in staying well • Identify warning signs • Planning for staying well • Set goals for the future	• Your Backup and Support Network • Staying Well Plan • Goals • Taking Stock • Staying in the Present (Sounds)
**Optional modules**		
	• Core beliefs	• Facing fears
	• Difficult moments (COVID-19 pandemic)	• Sleep difficulties
	• Managing grief	• My self-esteem and me
	• Managing anger	• Communication & relationships • Relaxation

#### Criteria for discontinuing or modifying allocated interventions {11b}

Participants in the follow-up surveys who report suicidal thoughts with some intent of acting on these thoughts will receive a closing statement at the end of their survey encouraging them to contact a mental health crisis number and will be told that they will be contacted by the clinical liaison at their university by the next workday. Similarly, participants in the guided iCBT who mention suicidal thoughts to their guide will be evaluated by their guide for intentionality and those with some intent of acting on these thoughts will be encouraged to contact the health crisis number, and the clinical liaison at their university will contact them. Those with a suicide attempt or unplanned hospitalization for any reason will be terminated from the intervention.

#### Strategies to assess and improve adherence to interventions {11c}

User engagement in Internet interventions can vary and can include user-related, content-related, and technology-related barriers and facilitators of engagement [43]. At the second week of inactivity, users will be sent a motivational email designed to improve empowerment and address treatment expectations and they will be offered a brief motivational video-conferencing session that will target user-related (e.g., expectations) and technology-related barriers.

#### Relevant concomitant care permitted or prohibited during the trial {11d}

Trial participants may receive any concomitant care. Moreover, students in all intervention arms on waitlist for university services may begin that treatment once they are off the waitlist. Receipt of concomitant treatment and type of treatment (e.g., psychotherapy, psychopharmacology) will be assessed at both follow-ups.

#### Provisions for post-trial care {30}

Access to SilverCloud will continue for 12 months after randomization for participants randomized to the two iCBT arms. Participants randomized to TAU will have the opportunity to access SilverCloud after 12 months.

### Outcomes {12}

The primary outcomes will be depression and anxiety symptom reduction and remission at 90 days and 12 months measured by the widely-used Patient Health Questionnaire-9 (PHQ-9) [44], Generalized Anxiety Disorder-7 Scale (GAD-7) [45], and the PHQ-Anxiety and Depression Scale (PHQ-ADS) [46]. The PHQ-9 is a self-report measure of depressive symptoms in the prior 2 weeks. Scores range from 0 to 27 with higher scores representing greater depressive symptomatology. The scale has both a sensitivity and specificity of 88% for identifying MDD [44]. The GAD-7 is a self-report measure of anxiety symptoms in the prior 2 weeks. Scores range from 0 to 21 with higher scores representing greater anxiety. Sensitivity and specificity for identifying GAD range from 70 to 92% [47]. The PHQ-ADS is a composite measure of the PHQ-9 and the GAD-7. Primary outcomes will be assessed both dimensionally and categorically. Consistent with standard practice, categorical thresholds for treatment response will be outcome scores less than 50% of baseline scores [48]. Remission will be defined as 0–4 on the PHQ-9 [49], 0–4 on the GAD-7 [45], and 0–9 on the PHQ-ADS [46].

Secondary outcomes also measured at 90 days and 12 months will be assessed only dimensionally (that is change in means/medians between groups). A secondary outcome will be impairment as measured by self-report questions based on the Army STARRS survey [50] of role impairment due to mental and physical health in four life areas in the prior 2 weeks. Scores in each area range from 0 to 10 with higher scores reflecting greater impairment. Additional secondary outcomes will include symptoms of comorbid disorders: panic disorder, social phobia, binge-purging disorders, PTSD, insomnia, suicidality, and frequency and quantity of alcohol and drug use. Panic disorder symptoms will be assessed with the Composite International Diagnostic Interview Screening Scales (CIDI-SC [51, 52]); social phobia with Diagnostic and Statistical Manual of Mental Disorders, 5^th^ Edition (DSM-5) diagnostic criteria [53]; binge/purge with questions from the Primary Care Evaluation of Mental Disorders (PRIME-MD) Patient Health Questionnaire (PHQ) [54]; PTSD with the six-item short-form PTSD Checklist for DSM-5 (PCL-5) screening scale [55]; and insomnia with a reduced version of the Insomnia Severity Index (ISI) [56]. Modified versions of the Columbia Suicidal Severity Rating Scale (C-SSRS) [57] and the Self-Injurious Thoughts and Behaviors Interview (SITBI) [58] will also be used to assess the degree of suicidal ideation and the number of plans and attempts. These scales have evidence of good concordance with blinded clinical diagnoses.

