## Objectives {7}

The overall goals of this study are to evaluate the effects of expanding treatment of CMDs among college students with symptoms of major depressive disorder (MDD) and/or generalized anxiety disorder (GAD) in two LMICs in Latin America (Colombia and Mexico) and to investigate the extent to which treatment outcomes could be improved by creating precision treatment algorithms to predict which intervention would be best for which students. The intervention will be a scalable and inexpensive intervention: iCBT. We have four specific objectives.

Objective 1: To carry out a year 1 pragmatic clinical trial with students in participating universities in Colombia and Mexico. Students will be recruited both from student mental health clinic waiting lists and from outreach emails sent to probability samples of other students. The student clinics have long waiting lists for all but the most urgent cases. Students on wait lists will be offered a two-thirds chance to receive iCBT immediately while staying on the list. The same offer will be made to students from the general student body recruited from emails. Interested students will be required to complete a baseline self-report assessment and, if eligible, to be randomized with equal allocation either to unguided iCBT (33%), guided iCBT (33%), or treatment as usual (TAU; that is, they will remain on the clinic waiting list until their appointment). Short-term aggregate intervention effects among students randomized across arms will be assessed 90 days after randomization and longer-term effects 12 months after randomization.

Objective 2: To use ensemble machine learning methods to predict heterogeneity of treatment effects of unguided iCBT versus guided iCBT versus TAU and develop a PTR to predict which students will respond best to which intervention. We will build a PTR for 90-day remission and a separate PTR for 12-month remission based on the year 1 pragmatic trial.

Objective 3: To carry out two additional trials in years 2 and 3 that build on the results of the first trial. Recruitment will be the same as in the first trial but randomization will be different in that a random 25% of participants will be randomized to the treatment estimated by the PTR for short-term response (the year 2 trial) or 12-month remission (the year 3 trial) based on the year 1 trial and the remaining 75% will be randomized with equal allocation across all 3 treatments.

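### Three overlapping scales are primary at two time points with none ranked first, and the outcome that trains and tests the precision treatment rule is not fixed

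*Protocol article*

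**What the plan says.** Outcomes {12} opens: "The primary outcomes will be depression and anxiety symptom reduction and remission at 90 days and 12 months measured by" the PHQ-9, the GAD-7 and the PHQ-ADS. It continues: "Primary outcomes will be assessed both dimensionally and categorically". Two categorical forms are then defined:

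- **Response:** "categorical thresholds for treatment response will be outcome scores less than 50% of baseline scores".
- **Remission:** a separate cut-off for each scale, 0–4 on the PHQ-9, 0–4 on the GAD-7 and 0–9 on the PHQ-ADS.

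The scales overlap: "The PHQ-ADS is a composite measure of the PHQ-9 and the GAD-7".

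Trial design {8} compares unguided iCBT, guided iCBT and TAU at both time points. It predicts that guided will beat unguided iCBT and makes no prediction for iCBT against TAU. The sample-size section bases power on remission, which it calls the form of greatest clinical importance, with two-sided 0.05 tests.

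For the PTR, Objective 2 states: "We will build a PTR for 90-day remission and a separate PTR for 12-month remission". Objective 3 and Trial design {8} describe the Trial 2 rule as optimising short-term response and the Trial 3 rule as optimising 12-month remission.

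**The concern.** A confirmatory trial needs to say which result decides it. Here the primary label covers every scale, form and time point, so a report could lead with whichever contrast came out best and still call it primary.

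The PTR raises a sharper problem. A rule has to be trained on one outcome, and this one then assigns treatment to 25% of the students in Trials 2 and 3. Three remission definitions and three response definitions are available, and the text moves between the two forms. As written, two choices could be made after data are seen: which Trial 1 PTR estimate to carry forward, and which outcome judges the rule in Trials 2 and 3.

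**Working it through.** **1. The plan's own power figure.** The sample-size section says fewer than 150 per arm suffice for aggregate effects, with remission about 30% against half that and response about 50% against half that.

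n = [1.96·√(2p̄q̄) + 0.8416·√(p1q1 + p2q2)]² / (p1 − p2)²

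For 30% v 15%: [1.96·√0.34875 + 0.8416·√0.3375]² / 0.0225 = 121 per arm (134 with continuity correction). For 50% v 25%: 58 (66). Allowing for loss, 121/0.85 gives 143 and 121/0.80 gives 152. The statement reproduces for loss up to about 18%, or about 10% with continuity correction. It is computed for one test at 0.05.

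**2. Count and error rate.** Three scales × two times × two or three forms, × three arm pairs. The counts are derived; the article does not state them. Independence would give 1 − 0.95^m, but the tests are strongly correlated, so the rate was simulated under no true difference.

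| Reading | Tests m | If independent | Simulated |
|---|---|---|---|
| Mean, response, remission (18 endpoints) | 54 | 0.937 | 0.60–0.76 |
| Mean and remission (12 endpoints) | 36 | 0.842 | 0.51–0.67 |
| Remission only (6 endpoints) | 18 | 0.603 | 0.40–0.52 |
| All 18 endpoints, one arm pair | 18 | 0.603 | 0.32–0.44 |
| One endpoint, three arm pairs | 3 | 0.143 | 0.11–0.13 |

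Settings: 500 per arm, 2,000–3,000 replicates, PHQ-ADS taken as the sum of the two scales, the protocol's cut-offs, unadjusted z tests. Assumed, not in the document: score means and SDs, and correlations of 0–0.8 between scales, 0–0.8 between follow-ups and 0–0.5 with baseline. Neither the eligibility cut-offs nor loss to follow-up were imposed. Further runs under assumed correlations gave 0.60–0.70 (54 tests), 0.49–0.58 (36) and 0.31–0.39 (one pair).

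**3. Do the three remission cut-offs form one definition?** No. PHQ-9 ≤ 4 with GAD-7 ≤ 4 forces a sum ≤ 8, so a joint rule would make 0–9 redundant. As separate definitions they can disagree:

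- PHQ-9 = 9, GAD-7 = 0 (sum 9): remitted on the GAD-7 and PHQ-ADS, not on the PHQ-9.
- PHQ-9 = 4, GAD-7 = 6 (sum 10): remitted on the PHQ-9 only.

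**4. Are response and remission interchangeable?** No. A PHQ-ADS change from 30 to 14 is a response (14 < 15) but not remission. A change from 16 to 9 is remission but not a response (9 is not below 8).

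**5. The PTR target, place by place.**

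- Objective 2: remission at both times.
- Objective 3 and Trial design {8}: response for the short-term rule, remission for the 12-month rule.
- Sample size: episode remission, and remitting from the primary outcomes in the plural.
- Additional analyses {20b}: the aggregate remission rate.

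None names a scale.

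**6. Baseline status.** The section on CMDs admits students with PHQ-9 ≥ 10, GAD-7 ≥ 10 or PHQ-ADS ≥ 20. A student with PHQ-9 = 12 and GAD-7 = 3 is eligible yet already in the GAD-7 remission range. With PHQ-ADS as the sum, every entry route gives at least 10, so no one enters in its 0–9 range.

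**7. Power for one named endpoint.** The assumed rates of 27.5% and 17.5% already allow for loss. SE = √[(0.275·0.725 + 0.175·0.825)/500] = 0.0262, and 0.10/0.0262 = 3.81. At 0.05: 3.81 − 1.96 = 1.85, power 97%. At 0.0167: 3.81 − 2.39 = 1.42, power about 92%.

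**The case against.** Five arguments count on the other side.

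- **The counts are a reader's construction, and response may not be primary.** True. The lead sentence names symptom reduction and remission only, hence the range of 12 to 18 endpoints. Only guided against unguided has a stated direction, and for one pair the rate is below one half. Trial design {8} still plans the three-arm comparison.
- **A multiplicity procedure may sit in the analysis plan, which is not shown.** This stands. The 0.05 level appears in the power section, and the analysis section promises 95% intervals. The absence of an adjustment rule is therefore not the point. The point is that the protocol itself designates all these outcomes as primary without order.
- **The form is prioritised.** Correct: remission is singled out. That still leaves three scales and two times, or 18 contrasts over three pairs.
- **Response may be used loosely for outcome.** Possible, and the abstract speaks of short-term outcomes. But Objective 3 sets response for year 2 beside remission for year 3 in one sentence, and Outcomes {12} gives response its own definition.
- **Trials 2 and 3 use separate samples, and Trial 1 cross-validates the rule.** This also stands. Choosing the training target after Trial 1 does not by itself inflate error in the later trials. Cross-validation, however, does not cover picking the best of several outcome definitions, and separate samples do not protect an evaluation outcome chosen once their data are seen.

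**Conclusion.** The primary outcome is badly fixed and the PTR target is inconsistent. Three overlapping scales are co-primary at two times with no order, and the short-term rule is aimed at remission in one place and at response in others, with no scale named in any of them.

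The 50–75% figure is conditional. It needs no true difference between any arms, unadjusted 0.05 tests on every contrast, and the assumed correlations. A reader might infer that the protocol commits to 54 unadjusted tests and that a chance finding is almost certain. The document supports neither: it states no such number or testing rule, and the independence figure of 94% ignores the strong correlation between the tests.

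The PTR half does not rest on the simulation. It follows from the definitions and the sections set side by side. The baseline argument for the PHQ-ADS assumes that the composite is the simple sum of its two parts, which the article does not spell out.

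**What to change.** Before outcome data are examined:

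1. Name one primary endpoint: remission on the PHQ-ADS (0–9) at 90 days. It covers both conditions, is the form used for powering, and no eligible student meets it at entry.
2. Test the three arm pairs with Holm.
3. Place PHQ-ADS remission at 12 months next in a fixed sequence, and write down the rule for passing to it. The simplest valid rule opens the 12-month tests only when all three 90-day contrasts are significant.
4. Make the other scales and forms secondary.
5. Correct Objective 3 and Trial design {8} so that both PTRs are trained on, and Trials 2 and 3 evaluated on, the same remission definition: 90 days for Trial 2, 12 months for Trial 3.

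The cost is wording in the protocol, the analysis plan and the registry. The other scales and forms lose confirmatory status. Power for 27.5% against 17.5% at 500 per arm falls from 97% to no less than about 92%, the value at 0.0167. No effect size is given for guided against unguided iCBT, so the loss of power there, and its effect on reaching the 12-month tests, cannot be stated.
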